### 2.4. Participants

This study will include patients over 18 years of age with a diagnosis of post-COVID-19 with new-onset moderate or severe pain. According to the World Health Organization (WHO) definition, patients present post-COVID-19 condition when they have persistent symptoms up to 3 months after the onset of the disease, lasting at least 2 months with no alternative diagnosis that explains these symptoms [6]. In addition, moderate or severe pain not limited to a specific anatomical district or origin will be assessed with a score greater than or equal to 3.5 using a Visual Analog Scale (VAS) [30]. Patients will be excluded if they present any of the following conditions: pulmonary, cardiac, neurological, vascular, or orthopedic pathologies that may limit the performance of the assessment and the intervention, cognitive impairment that prevents them from understanding and answering the questionnaires, or if they suffer reinfection by SARS-CoV-2. In addition, those patients with a history of severe or critical illness due to COVID-19 [6] and with pre-existing chronic pain according to the current International Association for the Study of Pain definition [31,32] will be excluded. Finally, patients who participated in other studies will also be excluded.

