#### 2.6.1. Experimental Group

The patients included in the experimental group will attend an 8-week PIM program in addition to standard medical care. The program is based on a previous study [27] and will be led by a physical therapist with experience in treating patients with chronic pain. This program will consist of 2 face-to-face sessions per week, and they will be asked to complete two sessions at home weekly. The first face-to-face session will be a group session with 3–6 participants, and the second face-to-face session will be individual. Both sessions will last approximately 1 h. In the group sessions, pain neuroscience education will be conducted. In the individual sessions, an individualized functional exercise program will be performed by each patient, as well as relaxation techniques. Patients will be asked to perform the functional exercises and relaxation techniques at home. Participants will be asked to record their compliance with the program and their progress.

Education in pain neuroscience is considered an important pillar in the comprehensive approach to persistent pain. Multiple studies support its use in patients with this complex symptom. This technique will allow the patient to better understand the complexity of the nervous system and the pain process. In this way, education in pain neuroscience will allow the therapist to provide the patient with the cognitive tools necessary to understand and adequately manage pain.

Pain neuroscience education will consist of group sessions in which simple explanations will be given on the difference between tissue damage and pain, especially in the case of chronic pain, central nervous system level nociception processing, pain modulatory signals, neuroplasticity and adaptability of other systems, and the relationship between stress, thoughts, emotion, and pain. The fundamental objective of this technique is to explain to the patient how the human being processes and perceives pain. The use of this technique will help the patients to understand their own experiences. Improving the patients’ knowledge of pain allows them to discard all the stigmas associated with persistent pain and will give them tools that will allow them to be active in their treatment.

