#### 2.6.2. Control Group

In addition to standard medical care, patients assigned to this group will receive a leaflet with information about the main post-COVID-19 condition symptoms. This is a control group that will not be controlled or monitored by a therapist.

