### 2.8. Sample Size Calculation

An a priori sample size was based on the minimum clinically important difference (MCID) of the BPI interference estimated to be 1.00 [50]. Using G*Power 3.1.9.2, we obtained a sample size of 49 participants, equally distributed between the treatment and control groups, based on a confidence level of 95% (α = 0.05) and a power of 80% (β = 0.2). Anticipating a 20% dropout rate, the total sample size was increased to ensure adequate statistical power and the resulting sample size was 30 participants per group.

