### 2.9. Statistical Analysis

Data will be analyzed using the Statistical Package of Social Science (SPSS) program for Windows (version 26 IBM, Armonk, NY, USA). Categorical data will be expressed as frequency (percentage). Continuous variables will be presented as mean and standard deviation (SD). The normality of the data will be first tested with the Shapiro-Wilk test. Characteristics of both groups will be compared using the Chi-square test for categorical variables. For continuous variables, the Student *t*-test will be used for those with a normal distribution and the Mann-Whitney U test for nonparametric variables. All effect sizes will be interpreted according to Cohen’s conventions: 0.3 = small, 0.5 = moderate, and 0.8 = large. A per-protocol analysis will be performed including participants who completed the treatment plan. Statistical significance will be set at *p* < 0.05.

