## 4. Discussion

The objective of this study will be to evaluate the early effects of the PIM program in post-COVID-19 condition patients experiencing persistent pain on pain intensity and interference, catastrophizing, kinesiophobia, and functionality. The results of this study are expected to demonstrate the effectiveness of the PIM program in reducing pain intensity levels and pain interference with daily activities compared to the control group. In addition, the results are expected to demonstrate the efficacy of the PIM program in reducing levels of catastrophizing, and kinesiophobia, as well as increasing levels of functionality. By conducting this study, we aim to provide clinicians with an intervention program with a comprehensive ability to address both the physical and psychological aspects of post-COVID-19 persistent pain.

The sample of subjects included in this study is expected to be similar to that of previous studies performed in post-COVID-19 patients, with similar anthropometric characteristics [51,52]. The higher prevalence of post-COVID-19 conditions in the female gender has been previously proven. These disparities in prevalence arise due to different symptomatic, inflammatory, and immunologic responses between men and women [53,54]. In addition, previous studies conducted on patients with post-COVID-19 conditions show that most patients with this condition are middle-aged, with median ages ranging from 45–55 years [7]. Thus, the sample included in this study is expected to include a higher proportion of women and have an average age of about 50 years.

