The methodological strengths of the research stand out in the detailed planning of the intervention protocol, which is easily reproducible in clinical settings. The individualized adaptation of the PIM, considering the physical limitations and progress of each participant, adds a distinctive element. Random allocation and blindness of the research assistant to the study hypothesis and patient assignment strengthen the internal validity of the study design. In addition, the inclusion of patients with moderate or severe pain (VAS ≥ 3.5 cm) and the exclusion of those with limiting medical conditions improve the homogeneity of the sample and the applicability of the results. In addition, for a better analysis of the PIM program, a record will be made of the adverse effects as well as the number of sessions completed by the study participants to assess feasibility and adherence.

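### The only analysis set stated is per-protocol on treatment completers, a criterion that bears essentially on the PIM arm, so the superiority comparison no longer rests on the randomised groups

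*Protocol article*

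**What the plan says.** Protocol article, section 2.9 (Statistical Analysis), gives the analysis set in one sentence: "A per-protocol analysis will be performed including participants who completed the treatment plan". No other set is named there or elsewhere in the article, and nothing marks this one as secondary. The three tables planned in section 3 refer to no other population.

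The two arms differ in what there is to complete:

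- PIM arm, section 2.6.1: "This program will consist of 2 face-to-face sessions per week, and they will be asked to complete two sessions at home weekly". Section 2.6 sets the duration at 8 weeks.
- Control arm, section 2.6.2: "patients assigned to this group will receive a leaflet with information about the main post-COVID-19 condition symptoms", on top of standard care. The same section adds: "This is a control group that will not be controlled or monitored by a therapist".

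The aim is superiority. Section 4 expects the results to show the "effectiveness of the PIM program in reducing pain intensity levels and pain interference with daily activities compared to the control group". That section also says that "a record will be made of the adverse effects as well as the number of sessions completed by the study participants"; the purpose given is feasibility and adherence.

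**The concern.** Randomisation makes the two groups comparable at the start. Restricting the analysis to people who went on to complete treatment selects them by something that happens afterwards. If the criterion can exclude many patients in one arm and almost none in the other, the analysed PIM group is a chosen part of those allocated to PIM, while the analysed control group is close to all those allocated to control. A difference at T2 may then reflect who stayed rather than what the programme did.

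The question matters here because the condition is painful and the programme asks for regular effort, so a link between how a patient fares and whether the patient finishes is plausible. Participants cannot be blinded (section 2.1) and all outcomes are self-reported (section 2.7.1), so the design already carries some risk of bias. Section 4 counts random allocation as a strength for internal validity, and a completers-only comparison gives part of that strength away.

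**Working it through.** **What completion means in each arm.** PIM: 8 weeks x (2 face-to-face + 2 home) = 32 sessions. Control: a leaflet and no sessions. The completion rule therefore has real content only for PIM. Controls can still leave the analysis if they have no T2 assessment.

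**The plan's own figure.** Section 2.8 gives a difference of 1.00 on BPI interference, α = 0.05, power 80% and 49 patients in total. No SD is given, so 49 cannot be reproduced directly. Solving the noncentral t power equation for 24 + 25 patients at 80% power, two-sided, gives d = 0.817, so SD = 1.00 / 0.817 = 1.22. One-sided, d = 0.721 and SD = 1.39. The illustration uses 1.22, with 2.0 as a wider alternative.

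**Inputs to the illustration.** From the article: 30 per arm and MCID 1.00. Assumed: no true effect, all 30 controls analysed, a proportion p of PIM patients not completing, and non-completers scoring g BPI points worse than completers. p = 20% borrows the article's dropout figure; it is not a stated non-completion rate.

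**Bias.** If the mean of the whole PIM arm is μ, the completers' mean is μ − p x g. With no true effect the control mean is μ. The spurious benefit is therefore p x g.

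- p = 0.20, g = 1: 0.20 x 1 = 0.20 points, and 0.20 / 1.00 = 20% of the MCID.

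**Type I error (normal approximation).** Analysed patients: 30 x 0.8 = 24 PIM and 30 control. Standard error = SD x √(1/24 + 1/30) = SD x 0.274.

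- SD 1.22: SE = 0.334; shift = 0.20 / 0.334 = 0.60 SE. P(Z > 1.36) + P(Z < −2.56) = 0.087 + 0.005 = 0.092.
- SD 2.0: SE = 0.548; shift = 0.20 / 0.548 = 0.365 SE. P(Z > 1.595) + P(Z < −2.325) = 0.055 + 0.010 = 0.065.

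Simulated t-tests agree: about 9% and 6 to 7%.

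**Range over the assumptions:**

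| Non-completion in PIM | Gap (BPI points) | SD | Spurious benefit | Two-sided type I error |
|---|---|---|---|---|
| 20% | 0 | any | 0 | 5% |
| 10% | 0.5 | 1.22 | 0.05 | about 5% |
| 20% | 1 | 2.0 | 0.20 | 6 to 7% |
| 20% | 1 | 1.22 | 0.20 | about 9% |
| 30% | 1 | 1.22 | 0.30 | 13 to 14% |

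**A second model.** Let completion and improvement have correlation ρ, and remove the 20% of PIM patients least inclined to complete. The shift is ρ x φ(z) / (1 − p) SD, with φ(z) = 0.280 at the 20% point, so ρ x 0.280 / 0.8 = 0.35ρ SD. For ρ = 0.3, 0.5 and 0.7 this is about 0.10, 0.17 and 0.24 SD towards PIM. Simulated type I errors are 6.4%, 9.7% and 15.3%. At ρ = −0.3 the shift is 0.10 SD against PIM. If the same outcome-related loss occurs in both arms, the mean bias is zero.

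**The case against.** The strongest reply is that the direction and size of the bias are not established. The article gives no completion rate, no reasons for stopping and no outcome gap between completers and others. Section 2.6.1 adapts the exercises to each patient's pain and ability, which may reduce stopping because of pain. With no link between completion and outcome there is no bias, and the illustration keeps every control, which is the unfavourable case. All of this stands. It limits what can be said about size, but it does not make completers the right primary population.

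A second reply is that an article condenses a longer plan, and a separate analysis plan might name another set. That would excuse silence. Here the article makes a choice, and nothing in it subordinates that choice to another analysis.

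A reader might also infer more than the text supports:

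- That patients are lost from the PIM arm alone. The sentence in section 2.9 names no arm, and controls without T2 would also be absent. Section 2.6.2 says controls are not monitored by a therapist, which does not mean that they are not assessed; section 2.6 schedules T1 and T2 for patients generally.
- That patients reinfected after randomisation would be removed as well, from the words "or if they suffer reinfection by SARS-CoV-2". Section 2.4 lists this among the eligibility exclusions, nothing applies it after randomisation, and it would not be specific to one arm.
- That the sample size makes no allowance for non-completers. Section 2.8 says only "Anticipating a 20% dropout rate" and does not define dropout, which may include them.
- That false-positive rates well above those in the table are to be expected. These need larger gaps between completers and non-completers, for which the article gives no support.

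**Conclusion.** The point holds. The sole analysis set stated for a superiority question is treatment completers, and the criterion bears essentially on PIM, so the comparison is not protected by randomisation. Bias towards PIM is likely if patients who do poorly stop early, but it is not certain.

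Under the main illustrative assumptions the bias is a fifth of the difference the trial is designed to detect, with a modest to moderate rise in type I error that depends strongly on the SD. These figures rest on assumed non-completion and outcome gaps and on an SD that the article does not state, so they show what is possible and are not an estimate for this trial. The point should be settled before follow-up ends, because T2 data not collected from non-completers cannot be recovered later.

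**What to change.** In section 2.9, make the primary analysis the comparison of all randomised patients in the arm to which they were assigned. State that T2 will be sought from everyone, whatever the number of sessions attended. Handle missing T2 with a method that uses the baseline data, for example a likelihood-based repeated-measures model or multiple imputation; the details can sit in the analysis plan. Keep the per-protocol analysis as a labelled sensitivity analysis, with completion defined in advance from the session counts that are already to be recorded.

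The cost is a change of wording, the effort of contacting PIM patients who stop, and possibly a smaller estimated effect. The change in analysis set itself calls for no additional patients.

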## 3. Results

The results will be published as a peer-reviewed article. The authors intend to generate 3 tables summarizing the main results of this article. The first will be the table of descriptive characteristics of the sample. The second table will present the data of the comparison between groups at baseline for the primary outcomes. The third table will present the post-intervention outcome data, showing the intragroup and between-group changes, and expressing the effect size using Cohen’s d. In addition, a figure with the flow diagram will be added.

## 4. Discussion

The objective of this study will be to evaluate the early effects of the PIM program in post-COVID-19 condition patients experiencing persistent pain on pain intensity and interference, catastrophizing, kinesiophobia, and functionality. The results of this study are expected to demonstrate the effectiveness of the PIM program in reducing pain intensity levels and pain interference with daily activities compared to the control group. In addition, the results are expected to demonstrate the efficacy of the PIM program in reducing levels of catastrophizing, and kinesiophobia, as well as increasing levels of functionality. By conducting this study, we aim to provide clinicians with an intervention program with a comprehensive ability to address both the physical and psychological aspects of post-COVID-19 persistent pain.

The sample of subjects included in this study is expected to be similar to that of previous studies performed in post-COVID-19 patients, with similar anthropometric characteristics [51,52]. The higher prevalence of post-COVID-19 conditions in the female gender has been previously proven. These disparities in prevalence arise due to different symptomatic, inflammatory, and immunologic responses between men and women [53,54]. In addition, previous studies conducted on patients with post-COVID-19 conditions show that most patients with this condition are middle-aged, with median ages ranging from 45–55 years [7]. Thus, the sample included in this study is expected to include a higher proportion of women and have an average age of about 50 years.

Although the published scientific evidence demonstrates the high prevalence of persistent pain in patients with post-COVID-19 conditions [55] and highlights the importance of future research efforts to focus on this aspect [56], to the authors’ knowledge this will be the first randomized control trial that focuses on developing an intervention to specifically address this symptom. To date, only one study in patients with post-COVID-19 conditions has included pain as a variable. The article by Hausswirth et al. [57] shows a significant improvement in the intervention group, which in this case underwent a four-week neuro-meditation intervention, compared to the control group. However, in other studies conducting pulmonary rehabilitation [58,59] the pain subscales show no improvement. These results highlight the need for specific rehabilitation programs that address the complexity of this symptom.

Regarding kinesiophobia, Nambi et al. [60] demonstrated that low-intensity aerobic exercise is more effective in improving kinesiophobia than high-intensity aerobic exercise in community-dwelling elderly with post-COVID-19 sarcopenia. However, it is important to note that both groups of patients underwent a program of low-intensity functional exercises similar to the one that will be carried out in our article. A previous study showed that athletes report less intense pain than sedentary individuals in response to an experimental pain procedure, catastrophizing a significant predictor of pain. However, catastrophizing was not a mediator in pain levels between athletes and sedentary individuals [61]. Additionally, Giacomo et al. highlight the relevance of combining rehabilitation and specific training considering the biomechanics of musculoskeletal pain [62]. Therefore, although more studies are needed to confirm it, low-intensity functional exercise seems to be a good therapeutic strategy to improve this variable in patients with post-COVID-19 conditions. Moreover, catastrophizing values will be collected in both groups.

With respect to functionality outcomes, many interventions have been developed to date to try to improve this variable in patients with this condition. These interventions are respiratory rehabilitation programs focused mainly on respiratory, functional, and quality of life variables. Some of these interventions have been shown to be beneficial in improving patient functionality [63,64,65,66]. In contrast, other studies have not found these differences in favor of the intervention group [67,68,69].

In addition to respiratory rehabilitation interventions, symptom control interventions have been developed in patients with post-COVID-19 conditions. In this type of intervention, the results regarding functionality are not consistent. In the study by Philip et al. [57] no significant improvements were found in the intervention group with respect to the control group. In contrast, in the study by Kuut et al. [70] significant differences were found with respect to the control group, but with a small effect size (Cohen’s d = 0.34). Further studies are needed to determine whether these types of interventions can help improve the functionality of patients with this condition.

The PIM program has been previously used in patients with osteoarthritis showing to be effective in reducing pain levels and functionality [27]. The results of our study are expected to achieve minimal detectable change for the Brief Pain Inventory and WHODAS 2.0 tools with complex scoring. If the expected results are achieved the PIM intervention program will prove to be effective in the management of persistent pain in patients with post-COVID-19 conditions.

Despite the positive results, this study has some limitations. Although the intervention proposed in this article fits the complexity of persistent pain post-COVID-19, the fact that it is a comprehensive intervention will make it difficult to determine the exact mechanisms behind patients’ improvement. Our intervention will include low-intensity functional exercise, relaxation exercises, and education in pain neuroscience, so we should consider the possible contribution of each component of the intervention. It would be interesting to design future research to investigate the efficacy of the different components of the overall intervention. Furthermore, the lack of participant blinding due to the nature of the intervention could introduce bias.

The methodological strengths of the research stand out in the detailed planning of the intervention protocol, which is easily reproducible in clinical settings. The individualized adaptation of the PIM, considering the physical limitations and progress of each participant, adds a distinctive element. Random allocation and blindness of the research assistant to the study hypothesis and patient assignment strengthen the internal validity of the study design. In addition, the inclusion of patients with moderate or severe pain (VAS ≥ 3.5 cm) and the exclusion of those with limiting medical conditions improve the homogeneity of the sample and the applicability of the results. In addition, for a better analysis of the PIM program, a record will be made of the adverse effects as well as the number of sessions completed by the study participants to assess feasibility and adherence.

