### 2.6. Intervention

The experimental group will be included in an 8-week PIM program. This program will include pain neuroscience education, functional exercise, consisting of low-intensity strengthening exercises, and relaxation techniques. The Template for Intervention Description and Replication (TIDieR) checklist [33] will be used. The control group will receive a leaflet. Patients in both groups will be allowed to take pharmacological treatment (paracetamol or non-steroidal anti-inflammatory drugs) if needed and under the prescription of a physician. Patients’ evaluations will be conducted at baseline (T1) and immediately post-intervention (T2).

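### Adverse effects are recorded as part of analysing the PIM programme, with no matching ascertainment described for controls, so the counts could not be read as an effect of PIM

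*Protocol article*

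**What the plan says.** Adverse effects appear only in section 4 (Discussion), among the strengths of the study: "a record will be made of the adverse effects as well as the number of sessions completed by the study participants". The same sentence ties this record to analysing PIM and gives feasibility and adherence as its aims. It names no arm.

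On contact with patients, section 2.6.1 says of the experimental group: "This program will consist of 2 face-to-face sessions per week, and they will be asked to complete two sessions at home weekly". The programme lasts 8 weeks. The same section adds: "Participants will be asked to record their compliance with the program and their progress". Of the control group, section 2.6.2 says: "This is a control group that will not be controlled or monitored by a therapist". Those patients receive a leaflet in addition to standard medical care.

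Some observation is common to both arms. Section 2.6 places evaluations at T1 and T2, and section 2.5 assigns them to a physical therapist who does not know the allocation. Section 2.7.1 makes BPI intensity and interference outcomes for the whole trial. The opening of section 2.7 asks patients, without limiting this to one arm, to keep a diary of their pain medication.

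**The concern.** Pain is the condition under study, and worsening pain is also a plausible effect of an exercise programme. Only a comparison with controls who are observed in the same way can separate the two. As described, the adverse-effect record serves the programme, and the programme arm has far more occasions on which an event can be noticed and written down.

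Two misreadings follow. Background events noted in PIM patients could be taken as harm from PIM, because few or none are noted in controls. Or genuine worsening caused by PIM could be dismissed as background, because no fair background count exists. Section 4 presents PIM as a programme for clinicians and as reproducible in clinical settings, so readers will look to the trial for some information on tolerability.

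**Working it through.** The article states no adverse-effect rate and no safety power, so there is no figure to reproduce. The check sets the sections side by side and then sizes the possible artefact under labelled assumptions.

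**What each arm is given**

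| Item | PIM arm | Control arm |
|---|---|---|
| Scheduled therapist contacts, T1 to T2 | 2 × 8 = 16 (section 2.6.1) | none described (sections 2.6, 2.6.2) |
| Record of compliance and progress | yes (section 2.6.1) | none described |
| Evaluation at T1 and T2, including BPI | yes (sections 2.6, 2.7.1) | yes (sections 2.6, 2.7.1) |
| Pain-medication diary | yes (section 2.7) | yes (section 2.7) |
| Adverse-effect record | yes, for analysing PIM (section 4) | not stated either way |

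The Discussion sentence couples adverse effects with sessions completed, feasibility and adherence. These concepts apply only to patients who have sessions, so a PIM-only record is the natural reading. If controls are also recorded, the first two rows still make capture unequal.

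**Size of the artefact (illustration)**

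Assumptions, none of them from the article: a weekly chance r of a reportable event, independent across weeks and the same in both arms; no effect of PIM; full capture in PIM; capture fraction c in controls. Arm size is 30 (section 2.8).

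- Probability of at least one event in 8 weeks: 1 − (1 − r)^8.
- r = 5%: 1 − 0.95^8 = 0.337, and 30 × 0.337 ≈ 10 patients.
- r = 10%: 1 − 0.90^8 = 0.570, and 30 × 0.570 ≈ 17 patients.
- Controls, c = 0: 0 recorded. Controls, c = 0.5: 30 × 0.337 × 0.5 ≈ 5 to 30 × 0.570 × 0.5 ≈ 9.
- Controls, c = 1: 10 to 17, and the artefact vanishes.

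With the 20% dropout that section 2.8 anticipates, 30 × 0.8 = 24 remain per arm. The PIM count becomes 24 × 0.337 ≈ 8 to 24 × 0.570 ≈ 14.

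**What equal ascertainment could show**

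For a two-sided 5% comparison of two proportions with 30 per arm, power is about 49% for 10% against 30%, 78% for 10% against 40%, and 39% for 20% against 40%. With 24 per arm these fall to about 41%, 68% and 32%. The rates are again assumed. Equal questioning removes the ascertainment artefact but does not make the trial a safety trial.

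**The case against.** A reader might infer three stronger things, none of which the article supports.

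- **That events are counted in one arm only.** The Discussion sentence refers to the study's participants and excludes nobody. One-arm recording is an inference from its stated purpose.
- **That controls go unobserved.** Section 2.6.2 denies them monitoring by a therapist, not all observation. They are evaluated at T1 and T2 by a blinded assessor.
- **That the trial can say nothing about worsening under PIM.** BPI intensity and interference are measured in both randomised arms, so net pain change has a comparator, and the diary bears on analgesic use. What is exposed is mainly transient or other events between visits.

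Two further objections have weight. This is a condensed article, so definitions, elicitation methods and tabulation of adverse events may sit in a full protocol; their absence from section 2.7 or from the three planned tables is not in itself a fault. The article also proposes no between-arm safety comparison: the sentence gives feasibility and adherence as its aims.

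These points narrow the concern but do not remove it. It rests on what is stated: a programme-linked record, intensive contact in one arm, and a control arm without therapist monitoring. Nor is the BPI a complete fallback. Section 2.9 plans a per-protocol analysis of those who completed the treatment plan, so a PIM patient who stopped because of worsening would leave that comparison.

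**Conclusion.** The point holds in a limited form. Followed as written, the article would produce adverse-effect counts that are ascertained unequally, whether controls are left out of the record or recorded with much less contact. Such counts could not be attributed to PIM.

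The direction of the artefact is predictable, towards more recorded events under PIM. Its size is not known. The illustration of 10-17 of 30 PIM patients, against 0 controls with no capture or about 5-9 with half capture, depends entirely on the assumed 5-10% weekly rate, full capture in PIM and the capture assumed in controls. Net pain change is unaffected by this problem, because the BPI is collected in both arms at the same times. The change is worth making because it is cheap and improves the only tolerability information the trial will provide.

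**What to change.** 1. At T2 the blinded assessor asks both arms the same fixed questions, worded without reference to any programme, about symptom worsening, new symptoms and unplanned care since T1.
2. State that only these answers are compared between arms. List events noted by the therapist separately, as descriptive for PIM only.
3. Report by arm, for all randomised patients with T2 data, the number whose BPI interference worsened by at least 1.00. Section 2.8 gives that value as the MCID for interference only, so it should not be carried over to intensity without justification. This uses data already collected.

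The cost is a few questions at an existing visit and a few lines in the results. There are three downsides. Recall over 8 weeks misses minor events, and may differ somewhat between arms because participants are not blinded and only PIM patients have therapist contact and a progress record. Answers may occasionally reveal the allocation to the assessor; asking these questions after the outcome questionnaires limits that risk. With 30 per arm the comparison should be presented as descriptive. If the questions are not added, the minimum is to state that the adverse-effect counts describe the PIM arm and support no comparison.
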